**Fig. 1 f0005:**
[figure not shown]
Example screens of Powerly app.

**Table 1 t0005:** Modules and personalization features included in the Powerly app.

Module	Personalization features
Reappraisal	Mood and affect tracking
Mental imagery	Name and icon selection
Self-efficacy	Progress tracking: number of completed exercises
Behavioral activation	Progress tracking: number of study days completed
Mindfulness	Pregnancy progress
Gratitude	Notifications

### Study design

2.2

We will conduct a two-arm RCT with repeated measures to evaluate the effects of Powerly compared to a control group receiving CAU. Assessments will occur at baseline, after four weeks of app use, and six weeks postpartum (Heller et al., 2020), see Fig. 2. The trial has been approved by the local ethics committee at the University of Zurich (approval #24.08.23) and has been registered with ClinicalTrials.gov (NCT06610552). The data collection will start in November 2024 until the desired sample size is reached. All procedures will be performed in accordance with the Declaration of Helsinki and its subsequent amendments. All participants will be asked to provide informed consent.

**Fig. 2 f0010:**
[figure not shown]
Study design and assessments.

### Participants

2.3

We will recruit participants mainly in Switzerland, Germany and Austria. Volunteers between 24 and 32 weeks pregnant will be included in the trial. Previous similar studies often included women in this range (Guo et al., 2020; Müller et al., 2020; Yang et al., 2019). Other inclusion criteria are being over the age of 18, owning an iPhone (due to technical limitations), and having sufficient fluency in German language. The exclusion criteria include high-risk pregnancies as self-reported, current substance abuse and history of psychiatric disorders such as bipolar disorder, schizophrenia, or other psychotic disorders, current use of professional face-to-face psychotherapeutic support, participation in other clinical trials or interventions at the same time.

### Outcomes and measures

2.4

To ensure the selection of outcome measures was rigorous and scientifically relevant for the population of interest, we based our choices on recommendations from comprehensive reviews that specifically focus on state-of-the-art assessments of maternal mental health and the quality of the mother-child bond (Beck and Gable, 2001; Clarke et al., 2024; Perrelli et al., 2014; Sinesi et al., 2019; Sit and Wisner, 2009).

#### Primary outcomes

2.4.1

The primary outcomes are related to mental health: (postpartum) depression, anxiety, and stress. These outcomes will be measured using the following validated instruments:

(a) DASS (Depression, Anxiety, and Stress Scales), a validated set of brief scales consisting of 21 items used to measure the severity of depression, anxiety, and stress symptoms (Lovibond and Lovibond, 1995),

(b) PDSS (Postpartum Depression Screening Scale), a comprehensive tool comprising 35 items designed to identify symptoms of postpartum depression, including aspects such as sleep and eating disturbances, insecurity, emotional lability, guilt, and shame (Beck and Gable, 2000).

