#### Sample size calculation

2.6.1

The sample size calculation for linear mixed models was determined using Cohen's d = 0.5, a mean effect size observed in prior studies investigating digital interventions in pregnant women, where the estimates have ranged from d = 0.4 to d = 0.65 (Heller et al., 2020; Jiao et al., 2019; Qin et al., 2022; Sawyer et al., 2019; Shorey et al., 2019). With a power of 80 % and a significance level of 0.05, the anticipated sample size was 67 participants per group. To account for dropouts, based on our previous studies with similar mobile apps (Marciniak et al., 2024b; Marciniak et al., 2024c), we will aim to include 70 participants per group.

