#### Primary and secondary outcomes

2.6.2

The adherence will be determined as the sum of all interactions with the app by each study participant, specifically: the number of completed entries, and the total time spent on engagements with Powerly.

The questionnaire scores will be calculated according to the manuals, including the relevant subscales. The primary statistical method for other primary and secondary outcomes will be linear mixed models, with time points (baseline versus follow-up I versus follow-up II) and group (Powerly versus CAU) as fixed effects, and participants as random effects. We will employ intention-to-treat analyses, in which we will include all randomized participants, regardless of their app use, complemented by as-treated analyses, including participants who will complete at least one module per day. If necessary, data transformation of dependent variables will be performed based on visual inspection of the data to ensure that the model assumptions are met. Secondary outcome measures will be utilized both as independent variables to assess the effectiveness of Powerly on these outcomes, and as moderators to further explore the Powerly's effect on primary outcome measures. Other covariates which may be used in the analysis include age, number of children, financial situation and stressors encountered by the participants.

The analyses will be conducted using R in R Studio.

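### At least four co-equal primary scores and no primary visit or order, but a sample size computed for one comparison at the full 0.05

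*Protocol article*

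**What the plan says.** Section 2.4.1 (Primary outcomes) of the protocol article opens with "The primary outcomes are related to mental health: (postpartum) depression, anxiety, and stress". It lists two instruments without ranking them. The DASS is "used to measure the severity of depression, anxiety, and stress symptoms", which gives three scores. The PDSS is "a comprehensive tool comprising 35 items designed to identify symptoms of postpartum depression", which gives at least one more.

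Section 2.6.2 adds that "The questionnaire scores will be calculated according to the manuals, including the relevant subscales".

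On timing, section 2.2 says: "Assessments will occur at baseline, after four weeks of app use, and six weeks postpartum". The mixed model in section 2.6.2 is specified "with time points (baseline versus follow-up I versus follow-up II) and group (Powerly versus CAU) as fixed effects, and participants as random effects". Neither section says which visit or contrast is primary.

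Section 2.6.1 takes a single effect size, d = 0.5, with 80% power and a "significance level of 0.05, the anticipated sample size was 67 participants per group", raised to 70 for dropout. It names no outcome or visit for that calculation and does not divide the 0.05.

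**The concern.** The primary-outcome section and the sample size section describe different trials. One has at least four primary scores of equal standing. The other has one comparison that receives the whole 0.05. Nothing in the article says which score, at which visit, the 0.05 and the 80% refer to.

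This matters because sections 1.2 and 1.3 make public release of the app depend on its being shown effective, and no rule says what would show that. If one significant score among several were enough, the chance of a false claim would exceed the stated level. If the scores were instead adjusted for multiplicity, the planned numbers would not give 80% power for each of them.

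**Working it through.** **Inputs from the article.** d = 0.5, power 80%, significance level 0.05, 67 per group before dropout and 70 after (section 2.6.1); three DASS scores plus the PDSS, so at least four primary scores (section 2.4.1); two follow-ups (section 2.2).

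**Assumptions.** Tests are two-sided. Each score is tested at 0.05, the only level given. Correlations between test statistics are not in the article, so a range is shown. Power uses a two-sample t-test without baseline adjustment.

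**Step 1: the plan's own figure.** For one two-sided comparison at 0.05, n = 2(1.960 + 0.842)²/0.5² = 62.8, so 63 per group; the exact t-test gives 63.8, so 64. Dividing 63.77 by the Mann-Whitney efficiency 3/π = 0.955 gives 66.8, so 67. The article does not say that this was the method, but it reproduces the figure. By t-test, 67 per group gives 81.9% power. Each of these is one comparison at the full 0.05; no division of alpha over four scores is visible in 67.

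**Step 2: false positives over four tests at 0.05 each, no true effect.**
- Independent: 1 − 0.95⁴ = 0.185.
- Correlated: simulation of equicorrelated normal statistics, 1,000,000 draws.

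| Assumed correlation | At least one significant, either direction | At least one significant, favouring the app |
|---|---|---|
| 0 | 18.5% | 1 − 0.975⁴ = 9.6% |
| 0.5 | 15.6% | 7.8% |
| 0.6 | 14.4% | 7.2% |
| 0.7 | 13.0% | 6.5% |
| 0.8 | 11.4% | 5.7% |

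The single-test reference is 5% for the middle column and 2.5% for the last.

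**Step 3: power if the four scores share 0.05.** Bonferroni level 0.05/4 = 0.0125. The noncentrality is 0.5 × √(67/2) = 2.89 at 67 per group and 0.5 × √(70/2) = 2.96 at 70. Power for one given outcome is then 64.1% at 67 per group and 66.5% at 70.

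**Step 4: power to find at least one.** If all four effects are 0.5 and the tests are independent, this is 1 − (1 − 0.641)⁴ = 98% at 67 per group. At a correlation of 0.6 it is about 87% to 88%, and at 0.8 about 81% to 82% (the lower figure in each pair uses the t critical value, the higher the normal one).

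**Step 5: number of tests.** A joint group-by-time test per score gives four tests. Separate contrasts at the two follow-ups would give more and raise the rates in step 2. How many more depends on when the PDSS is given, and that schedule is in Fig. 2, which is not shown.

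**The case against.** The article never says that each score is tested at 0.05, that no adjustment will be made, or that one significant score is enough. Multiplicity handling and the decision rule are often left to an analysis plan, and none is shown. This part stands: the error rates in the working are conditional, and silence about adjustment is not by itself a finding. But choosing the primary outcomes and fixing the sample size are protocol decisions, and this article makes both. A later Bonferroni or Holm adjustment would leave less than 80% power for a given outcome at its strictest step.

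Three stronger readings are tempting, and the documents do not support them:

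- **Eight primary tests.** A reader might count four scores at two visits. The model in section 2.6.2 allows one joint test per score. The PDSS is a postpartum scale, and follow-up I falls before birth for most women enrolled at 24 to 32 weeks. Eight is not established.
- **An 18.5% chance of false success.** That figure includes significant results against the app, which could not support a claim of effectiveness. In the app's favour the rate is about 6% to 10%.
- **Only 64% power for the trial as a whole.** That is power for one named outcome at 0.0125. Under an any-one rule, power with Bonferroni is about 81% or more in the cases examined. Adjustment for baseline would also help scores measured at baseline: at an assumed baseline correlation of 0.5, with d on the raw SD, power at 0.0125 is about 79%.

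It is also fair to say that the stated aim covers postpartum anxiety as well as depression, so choosing the PDSS alone would leave part of the aim outside the primary test.

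**Conclusion.** The concern holds in a limited form. The article declares at least four co-equal primary scores with no primary visit or hierarchy, and sizes the trial for one comparison at the full 0.05. The stated 0.05 and 80% are therefore not tied to any defined test.

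If any significant primary score counts as showing effectiveness, the error over four tests is two to nearly four times nominal: about 11% to 18.5% against 5% in either direction, or about 6% to 10% against 2.5% in the app's favour. This rests on 0.05 per test, an any-one rule and assumed correlations from 0 to 0.8. The first two are inferred and not stated; the text does not exclude them. Separate tests at both visits would raise the rates by an amount that cannot be settled from the article.

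If the four scores share 0.05 by Bonferroni, power for a given outcome falls from about 82% to about 64% at 67 per group (67% at 70), by unadjusted t-test.

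**What to change.** Before unblinded results are seen, name one primary score and one visit, and state that the 0.05 and 80% in section 2.6.1 apply to that test. One option is the PDSS total at six weeks postpartum. DASS anxiety at the same visit would come next, since the aim names postpartum anxiety beside depression, and the remaining DASS scores would follow in a stated fixed order, each tested at 0.05 only if the one before it succeeds. Label follow-up I and all subscales secondary, and say which contrast of the mixed model carries the primary test.

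If all four scores must stay co-primary, use Holm and restate the power per outcome (about 64% at the first step with 67 per group, on the unadjusted t-test). Do not enlarge the sample for this.

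The cost is an amendment to the protocol and registry wording. The downside of the fixed sequence is that a later outcome can be claimed only if every earlier one succeeds, so the order should be chosen with care.

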#### Secondary outcomes

2.4.2

Secondary outcomes are divided into three categories:

##### Emotion regulation and resilience outcomes

2.4.2.1

(c) CERQ (Cognitive Emotion Regulation Questionnaire), which comprises 36 items assessing the strategies individuals employ to manage their emotions, including positive reappraisal, acceptance, rumination, and putting into perspective, among others (Garnefski and Kraaij, 2007).

(d) PASS-C (Positive Appraisal Style Scale – content-focused), comprises of fourteen items and measures person's general style of evaluating stressors (Petri-Romão et al., 2024).

(e) BRS (Brief Resilience Scale) measures resilience operationalized as an outcome of the process of adaptation to adversity, using five questions (Smith et al., 2008).

(f) GSE (General Self-Efficacy Scale) evaluates an individual's optimistic self-belief in their capability to handle difficult tasks, challenges, and adversities, through ten items (Schwarzer and Jerusalem, 1995).

##### Mother & child outcomes

2.4.2.2

(g) BSS-RI (Birth Satisfaction Scale – Revised Indicator), which assesses the subjective experience of labor, including aspects of anxiety, stress, feelings of control, and support, using six items (Martin et al., 2017).

(h) MFA (Maternal-Fetal Attachment Scale), the 24-item scale evaluates the bond between mother and fetus during pregnancy. It includes questions about interactions with the fetus, attributing characteristics to the fetus, and role-taking, among others (Cranley, 1981). The MFA will be administered at baseline and the first follow-up.

(i) PBQ (Postpartum Bonding Scale), the 25-item questionnaire measures the quality of the bond between the mother and her infant. It includes factors such as the general bonding factor, anxiety about the baby, and rejection (Brockington et al., 2006). The PBQ will replace the MFA at the second follow-up.

##### EMI Acceptability

2.4.2.3

(j) mARM (mobile Agnew Relationship Measure), which evaluates the therapeutic alliance between the app and the user through 25 items. It covers topics such as confidence, openness, user initiative, and partnership (Berry et al., 2018).

(k) uMARS (user version of the Mobile Application Rating Scale), tool used for assessment of the feasibility of the app, including aspects of engagement, aesthetics, functionality, and the quality of information provided in the EMI, with 20 questions (Stoyanov et al., 2016).

(l) Adherence – the number of interactions with the app by each of the participants, i.e., the number of completed entries in the app, and the total time spent on engagements with Powerly.

The baseline assessment will be complimented with (m) BFI-10 (Big Five Inventory-10), which assesses the five major dimensions of personality (openness, conscientiousness, extraversion, agreeableness, and neuroticism) with ten items (Rammstedt and John, 2007) and (n) PMH (Positive Mental Health scale) including nine items to measure specifically positive mental well-being (Lukat et al., 2016). The inclusion of these measures allows for exploratory analyses aimed at potentially customizing app delivery in the future research based on individual personality and mental well-being traits.

Refer to Fig. 2 for a detailed schematic representation of the study design and the timing of assessments.

### Procedure

2.5

Participants will be recruited through multiple channels, primarily via gynecology wards in hospitals, gynecology and midwifery practices, and other pregnancy-related services such as birthing classes, prenatal yoga, and parenting workshops. To ensure a diverse sample with various backgrounds, we will also promote the study online through social media platforms targeting pregnant women. Volunteers interested in participating in the study will complete a brief online form providing basic demographic information (age, gender, education) and respond to questions regarding exclusion criteria. Those who meet the inclusion criteria will be contacted by a researcher and assigned a personal code for use throughout the study. The baseline assessment will be conducted online to accommodate participants who may have difficulties traveling while pregnant. Group allocation will be determined using a randomization algorithm generated by a National Institutes of Health clinical trial randomization tool, and the study personnel will be blinded to the group allocation. Participants in the intervention group after completing the baseline questionnaires, will receive instructions on how to download Powerly. They will be encouraged to use the app daily for 28 days, at least once per day, and will be invited to complete the questionnaires again. The duration and frequency of the intervention are based on previous research on CBT-based apps, which found that a four-week period with at least one interaction per day is both common and sufficient to achieve significant improvements in mental health outcomes while ensuring high adherence to the intervention and low drop-out rates (Birney et al., 2016; Marciniak et al., 2020). Participants in the CAU group will complete baseline questionnaires and be informed that they will receive access to Powerly six weeks postpartum. After 28 days, they will be invited to complete the questionnaires again, in a similar manner to Powerly group. Both groups will be contacted around their expected delivery date to confirm the birth date, and again six weeks postpartum for a final follow-up. After this, the CAU group will receive access to Powerly.

We do not anticipate any adverse effects caused by Powerly. However, to ensure early detection of any mental health distress in this vulnerable population, participants will have the option to contact the principal investigator via email throughout the trial. If participant's scores on the Postpartum Depression Screening Scale exceed the clinical threshold, they will be contacted and offered access to professional psychological services in their area.

### Analysis

2.6

#### Sample size calculation

2.6.1

The sample size calculation for linear mixed models was determined using Cohen's d = 0.5, a mean effect size observed in prior studies investigating digital interventions in pregnant women, where the estimates have ranged from d = 0.4 to d = 0.65 (Heller et al., 2020; Jiao et al., 2019; Qin et al., 2022; Sawyer et al., 2019; Shorey et al., 2019). With a power of 80 % and a significance level of 0.05, the anticipated sample size was 67 participants per group. To account for dropouts, based on our previous studies with similar mobile apps (Marciniak et al., 2024b; Marciniak et al., 2024c), we will aim to include 70 participants per group.

#### Primary and secondary outcomes

2.6.2

The adherence will be determined as the sum of all interactions with the app by each study participant, specifically: the number of completed entries, and the total time spent on engagements with Powerly.

The questionnaire scores will be calculated according to the manuals, including the relevant subscales. The primary statistical method for other primary and secondary outcomes will be linear mixed models, with time points (baseline versus follow-up I versus follow-up II) and group (Powerly versus CAU) as fixed effects, and participants as random effects. We will employ intention-to-treat analyses, in which we will include all randomized participants, regardless of their app use, complemented by as-treated analyses, including participants who will complete at least one module per day. If necessary, data transformation of dependent variables will be performed based on visual inspection of the data to ensure that the model assumptions are met. Secondary outcome measures will be utilized both as independent variables to assess the effectiveness of Powerly on these outcomes, and as moderators to further explore the Powerly's effect on primary outcome measures. Other covariates which may be used in the analysis include age, number of children, financial situation and stressors encountered by the participants.

The analyses will be conducted using R in R Studio.

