#### Phase II – Development of leading therapeutic agents

2.1.2

Following the literature review, we integrated PCR and mental imagery as primary therapeutic components within Powerly.

Positive cognitive reappraisal was selected as a key stress resilience factor (Carlson et al., 2012; Kalisch et al., 2015). It has been successfully implemented in various therapeutic settings and proven effective in diverse contexts, as indicated by previous literature (Morello et al., 2023; Riepenhausen et al., 2022). Furthermore, individuals who can flexibly apply PCR techniques in response to the varying emotional demands of stressful situations tend to experience lower levels of perceived stress (Marciniak et al., 2024a). Given that pregnancy and early motherhood are often perceived as particularly stressful periods (Loomans et al., 2013), incorporating this component is essential. Within Powerly, pregnant individuals will be prompted to recall a recent stressful event and generate three possible reappraisals for this event. These reappraisals might include identifying unexpected benefits, learning something from the event, or considering advice they would give to someone facing a similar challenge. This particular module has been tested in two RCTs on a population of young adults in Switzerland who initially had a lower tendency to use PCR. It was found to be effective in increasing the use of PCR and in reducing anxiety symptoms, and highly feasible as indicated by over 80 % adherence (Marciniak et al., 2023).

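### Adherence is defined only as total entries and total time, so it cannot show whether women used Powerly daily for 28 days as asked

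*Protocol article*

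**What the plan says.** The protocol article defines adherence twice, in the same form. Section 2.4.2.3 (EMI Acceptability) lists it as "the number of completed entries in the app, and the total time spent on engagements with Powerly". Section 2.6.2 (Primary and secondary outcomes) says "The adherence will be determined as the sum of all interactions with the app by each study participant" and then names the same two quantities. Neither place states a period over which use is counted, a per-day unit or a denominator, and neither says what an entry is.

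Two other statements describe use by the day. Section 2.5 (Procedure) says of the intervention group: "They will be encouraged to use the app daily for 28 days, at least once per day". Section 2.6.2 describes the intention-to-treat analysis as "complemented by as-treated analyses, including participants who will complete at least one module per day".

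Table 1 lists six modules in one column and personalization features in another. The features include "Mood and affect tracking" and a counter of study days.

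**The concern.** The request made to participants concerns regularity: something on each day for four weeks. The outcome measures volume. A woman's volume does not reveal on how many days she used the app, so the adherence result could not be read against what she was asked to do.

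The same section also holds two yardsticks for use that do not convert into each other. The outcome counts entries and time; the as-treated set counts modules by day. A reader given the adherence totals could not tell how many women came close to the as-treated criterion.

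Adherence is one of three acceptability measures (with therapeutic alliance and app rating), and the Discussion presents engagement without incentives as a strength of the design. What is at stake is whether the trial can answer its own question about acceptability in unpaid, near-real-life use.

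**Working it through.** The article gives no adherence figure, so there is nothing to reproduce. The check is whether the stated measure separates women who used the app as asked from women who did not.

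**Inputs**
- Stated measure: total completed entries (sections 2.4.2.3 and 2.6.2). Total time is also cumulative and has the same limitation.
- Use asked for: at least once a day for 28 days (section 2.5).
- As-treated rule: at least one module a day (section 2.6.2), read here as every one of the 28 days because no tolerance is stated.

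**Comparison measure:** days with at least one completed module ÷ 28.

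The users below are hypothetical. Each completes modules only, all within the 28 days.

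| Pattern of use | Total entries | Days with a module | Share of 28 days | Meets as-treated rule |
|---|---|---|---|---|
| One a day for 28 days | 28 | 28 | 28/28 = 100% | yes |
| Two on one day, one on each of 26 others | 2 + 26 = 28 | 27 | 27/28 = 96% | no |
| Two a day for 14 days, then none | 2 × 14 = 28 | 14 | 14/28 = 50% | no |
| 10, 10 and 8 on three days, then none | 10 + 10 + 8 = 28 | 3 | 3/28 = 11% | no |

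One value of the stated outcome therefore covers 11% to 100% of days used, and both sides of the as-treated rule.

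**At group level** (an invented split of the 70 women planned for the Powerly arm): 35 make two entries a day for 28 days (56 each), and 35 make one a day for three days and stop (3 each).
- Mean entries = (35 × 56 + 35 × 3)/70 = (1,960 + 105)/70 = 29.5, which is above 28.
- Days used = (35 × 28 + 35 × 3)/(70 × 28) = 1,085/1,960 = 55%.

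The article does not say that adherence will be summarised by a mean. The example shows only that a total can look complete when half the group stopped on day 3.

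**The case against.** The strongest reply is that a condensed article may leave the log cut-off, the meaning of an entry and the coding of non-downloaders to a full protocol or analysis plan. The 28-day window can be inferred from the Abstract and section 2.5. Total entries and total time are recognisable measures of dose, and daily use is a floor, so extra use is legitimate. The as-treated rule already identifies strictly daily users and would exclude a woman who did everything in three days.

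Much of this stands. The window and the meaning of an entry would, on their own, be details to clarify. The as-treated rule does give the trial one per-day criterion. But that rule only sorts women into or out of an analysis set; it does not report how much of the requested use took place. The choice of totals is not silence: the article states it in two places, and an analysis plan that followed it would carry the mismatch forward.

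A reader might infer more than the text supports:
- **That intensive short-term users would be classed as adherent.** No threshold is stated, so nobody is classed. Different patterns merely share a score.
- **That a count and a duration are added into one number.** The wording reads naturally as two totals per woman.
- **That a woman who only logs mood would score 28.** This holds only if a mood log is an entry. The article does not say so, and Table 1 lists mood tracking apart from the modules.
- **That idle screen time is counted.** Nothing in the article says this.
- **That use after day 28 inflates the total.** The article does not say that access or counting continues beyond then.
- **That the result falls short of an 80% benchmark.** Section 2.1.2 calls the reappraisal module "highly feasible as indicated by over 80 % adherence" in earlier trials. It does not define that adherence or set it as a target for Powerly.

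**Conclusion.** The point holds as a poorly chosen definition. The stated totals cannot show whether Powerly was used as asked, and they do not correspond to the as-treated rule in the same section. In the worked cases, 28 entries fits anything from 3/28 (11%) to 28/28 (100%) of days. That range rests on hypothetical users, all of whose entries are completed modules within the 28 days; it needs no assumption about mood logs or later use. How far real use will be uneven cannot be known from the article.

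The consequence is confined to a secondary acceptability outcome measured in the Powerly arm. The primary intention-to-treat comparison and the sample size are unchanged. The change is worth making because it bears on a question the trial says it will answer.

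**What to change.** - Make the main adherence measure the number of days, out of the 28 after baseline, with at least one completed module, divided by 28. Calculate it for every woman allocated to Powerly, with 0 for those who never download the app.
- Keep total entries and total time as two separate descriptive measures over the same 28 days.
- State whether a mood log counts as an entry.

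With this measure, the as-treated rule (read as every day) becomes the top of the adherence scale, 28/28, so the two can be reported together.

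The cost is a wording change and minor recoding of app logs. The as-treated rule already requires module data by day, and Table 1 shows that the app tracks study days. The downside is that the reported figure may look less favourable than a total would.

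### The primary mixed model names no group-by-time term, baseline adjustment or treatment contrast; fitted as written, it recovers only two thirds of a constant effect for outcomes measured at all three visits

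*Protocol article*

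**What the plan says.** The protocol article, section 2.6.2 (Primary and secondary outcomes), gives one model for the questionnaire outcomes: "linear mixed models, with time points (baseline versus follow-up I versus follow-up II) and group (Powerly versus CAU) as fixed effects". Each participant has a random effect. The section spells out the three levels of time, and baseline is one of them. No section names a group-by-time interaction, uses the baseline score as a covariate, or says which coefficient or contrast is the treatment effect.

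Section 2.2 (Study design) sets the visits: "Assessments will occur at baseline, after four weeks of app use, and six weeks postpartum". Section 2.5 (Procedure) shows that baseline comes before any exposure to the app: "Participants in the intervention group after completing the baseline questionnaires, will receive instructions on how to download Powerly".

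Section 2.6.1 (Sample size calculation) says the calculation is for linear mixed models. It was "determined using Cohen's d = 0.5, a mean effect size observed in prior studies investigating digital interventions in pregnant women", and "With a power of 80 % and a significance level of 0.05, the anticipated sample size was 67 participants per group". For dropout, "we will aim to include 70 participants per group".

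**The concern.** If time and group are the only fixed effects, the model has one treatment parameter, the group coefficient. That parameter is the between-arm difference averaged over all visits, including one at which randomisation makes the expected difference zero. Three things follow for an outcome with a baseline:

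- the estimate is pulled toward zero;
- the model has no separate parameter for four weeks or for six weeks postpartum, although preventing postpartum depression and anxiety is the app's stated purpose;
- the test no longer has the effect size on which the sample size rests.

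If the authors intend an interaction, the text still does not say which contrast is the result. Two analysts could follow the same sentence and report different primary estimates.

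**Working it through.** **Inputs from the article.** Three visits, one before treatment and two after (2.2, 2.5); d = 0.5, from a quoted range of 0.4 to 0.65; 80% power; significance level 0.05; 67 per group before dropout (2.6.1). The article gives no within-person correlation ρ. I assume 0.3, 0.5 and 0.7, equal between all pairs of visits as a random intercept implies, with unit variance, complete data and a two-sided test.

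**The plan's own figure.** A two-sided two-sample t-test at d = 0.5 and 80% power needs 63.77, so 64 per group. Dividing by the rank-test efficiency 3/π = 0.955 gives 63.77 / 0.955 = 66.8, so 67. This reproduces the stated number, but the route is inferred. The article gives no correlation or number of measurements for a mixed-model calculation. A plain t-test with 67 per group has 82% power.

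**Group coefficient, literal model.** With complete data it estimates (0 + d1 + d2) / 3, whatever ρ is. For d1 = d2 = 0.5 this is 1.0 / 3 = 0.333, one third below 0.5. In 150 simulated mixed-model fits (ρ = 0.5, 70 per group) the mean coefficient was 0.32. With a time-by-group interaction, the two follow-up contrasts against baseline were both 0.49.

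**Power at 67 per arm, effect 0.5 at both follow-ups.**
- Literal model: the variance of a three-visit mean is (1 + 2ρ) / 3. At ρ = 0.5 the SD is √0.667 = 0.816 and the standardised effect 0.333 / 0.816 = 0.408.
- Interaction contrast (change from baseline): SD = √(2(1 − ρ)). At ρ = 0.5 this is 1.0, and the standardised effect is 0.5.
- Baseline-constrained or baseline-adjusted contrast at one follow-up: SD = √(1 − ρ²). At ρ = 0.5 this is 0.866, and the standardised effect is 0.577.

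| Assumed ρ | Literal group coefficient | Interaction contrast | Baseline-constrained or adjusted |
|---|---|---|---|
| 0.3 | 75% | 68% | 85% |
| 0.5 | 65% | 82% | 91% |
| 0.7 | 57% | 96% | 98% |

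**Other effect patterns, literal model.**
- Effect of 0.5 at one follow-up only: 0.5 / 3 = 0.167, with 22% power at ρ = 0.5.
- 0.5 then 0.25: 0.75 / 3 = 0.25, which is 50% below follow-up I and 0% below follow-up II.
- 0.4 then 0.65: 1.05 / 3 = 0.35, which is 12.5% below follow-up I and 46% below follow-up II.

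**Dropout.** Baseline gains weight when later visits are lost. Under random monotone dropout and a constant effect, the shrinkage is 34–35% at the dropout implied by 67 and 70 (1 − 67/70 = 4.3%), and 36–37% at 10%.

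**Which outcomes.** MFA is given at baseline and the first follow-up only, so its literal coefficient for a 0.5 effect is 0.5 / 2 = 0.25. PBQ is given only at the second follow-up, and birth satisfaction cannot have a baseline before the birth. The timing of PDSS is left to Fig. 2, which is not available here.

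**The case against.** The strongest reply is that the sentence sorts factors into fixed and random and does not claim to be a full model formula. It does not call the model additive, and an interaction of two fixed factors is itself a fixed effect. The same paragraph plans to use secondary outcomes as moderators of the app's effect, which requires interaction terms that it also leaves unwritten. A fuller analysis plan may exist. This stands: a reader might infer that the authors have committed to a main-effects-only model, and the article does not support that. What it does show is a named primary method, with its factors and levels listed, that does not identify the treatment effect.

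Four further limits also stand.

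- A reader might infer that the app's effect will always be understated by a third or more. One third holds against a constant effect or the mean of the two follow-up effects; against a single follow-up it can be smaller or nil.
- Outcomes without a baseline are untouched. That includes the primary PDSS if it is given only postpartum.
- Under randomisation, chance baseline imbalance adds noise and not bias, and the literal test keeps its validity under the null. The risk is attenuation, not false-positive efficacy.
- The power loss depends on the assumed correlation. At 0.3 a plain interaction contrast (68%) does worse than the literal model (75%), so adding an interaction alone is not a sure repair.

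**Conclusion.** The point holds in a bounded form. As written, the primary model names no group-by-time term, baseline adjustment or treatment contrast. Followed literally for an outcome with all three visits, it estimates two thirds of a constant post-baseline effect: 0.33 where the sample size assumes 0.5. That ratio is algebra for complete data and does not depend on the correlation. The power figures of about 75%, 65% and 57% do depend on it, and they also assume equal correlations, complete data and a constant effect. DASS-21 is the primary instrument most likely to be affected, provided it is given at every visit.

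The case for change does not rest on guessing the authors' intention. At each correlation examined, the baseline-constrained or baseline-adjusted contrast has more power than both the literal model and the plain interaction contrast.

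**What to change.** Replace the model sentence in section 2.6.2 with wording such as: *Outcomes measured at baseline and at follow-up are analysed by a linear mixed model with time and group-by-time as fixed effects, baseline means constrained equal between arms, and participant as random effect (or with the follow-up scores as outcomes and the baseline score as covariate). The treatment effect is the between-arm difference at each follow-up. The primary follow-up for each outcome is [to be named]. Outcomes measured at one visit only are compared between arms at that visit.*

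The sponsor should name the primary follow-up for each outcome before any outcome data are examined; the article lists both follow-ups and ranks neither. The cost is a few sentences of analysis text, with no new data, visits or participants.
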